### Who will take informed consent? {26a}

Prior to the initiation of the study, research assistants (at least 2 research assistants per centre) will be trained regarding the details of this study protocol, to ensure smooth operations and consistency. Protocol modifications are not to be expected. When patients are identified and diagnosed with acute HZ, research assistants will be informed and asked to screen patients for eligibility. Eligible patients who are willing to participate will be provided a verbal explanation of the written consent. Patient queries will be answered and each patient interested in the study will have sufficient time to decide whether to participate in this study, and written informed consent will be obtained from willing participants.

### Additional consent provisions for collection and use of participant data and biological specimens {26b}

The consent form will include the permission of collection and use of participant data, should the participants decide to withdraw from the trial, along with the permission to share relevant data with members of regulatory authorities, when necessary. This trial does not involve the collection of biological specimens.

## Interventions

### Explanation for the choice of comparators {6b}

For patients assigned to the control arm, 1000 mg valacyclovir will be administered three times a day for 7 days. The antiviral therapy has been recommended as a standard therapy for HZ and widely applied in previous studies [18, 19, 21]. The mechanism involves hastening the resolution of lesions, preventing the formation of new lesions and decreasing the severity of acute pain [13]. The analgesics, including non-opiates, weak opiates and strong opiates, will be provided as needed.

### Intervention description {11a}

For participants assigned to the duloxetine arm, 20 mg duloxetine (YouBiLuo®, NHWA, China) will be orally administered once daily, after breakfast. If the patient’s VAS score reaches 0 within the first week, duloxetine will be discontinued; otherwise, it will be increased to 40 mg once daily, for the second week. If the VAS score reaches 0 within the second week, duloxetine will be tapered down to 20 mg once daily for a week and discontinued; otherwise, it will be increased to 60 mg once daily and maintained until a VAS score of 0 is obtained, or until the end of the 10th week. Then, duloxetine will be tapered to 40 mg once daily for a week, followed by 20 mg once daily for a week, and then discontinued. For participants who develop adverse effects, the dose will be adjusted to the last tolerated level. Participants in the control arm will not be given duloxetine during the 12-week treatment period.

### Criteria for discontinuing or modifying allocated interventions {11b}

All the AEs (adverse events) of the study will be closely monitored, properly documented in detail, and reported to the ethics committee with the aims of resolving the condition or even dissolution of the study if necessary.

### Strategies to improve adherence to interventions {11c}

Once assigned to one of the two study groups, a pharmacological protocol will be given as per allocation. Physicians and research assistants will be responsible for instructing participants to follow the protocols correctly, and to ensure adherence to interventions. After recruitment, each participant will be given a pain diary (PD), in which all outcomes can be recorded by the participants themselves during the study period. The specific recording criteria are as follows: (i) the VAS score will be recorded every morning before breakfast, (ii) AEs and consumption of each analgesic will be recorded every evening before bed, and (iii) the 12-item Short-Form Health Survey (SF-12), Patient Global Impression of Change Scale (PGIC) and Sleep quality as measured by the Pittsburgh Sleep Quality Index (PSQI) will be self-assessed at baseline and upon completion of weeks 4, 8, and 12. During the study period, the research assistants will monitor the participants’ completion of the PDs and deliver reminders as necessary through telephone calls or social media. At the end of week 12, the PDs will be collected by the research assistants and stored by the Data Safety Monitoring Board (DSMB). The research assistants will be available 24 h a day, 7 days a week, to answer any questions related to the study.

### Relevant concomitant care permitted or prohibited during the trial {11d}

For all participants, 1000 mg valacyclovir will be administered three times a day for 7 days, and analgesics will be given according to the three-step World Health Organization (WHO) pain ladder [27]. Non-opioids will be preferred for mild pain, weak opioids plus non-opioid analgesics will be recommended if moderate pain is developed, and strong opioids plus non-opioids will be provided for severe pain. All selected analgesics will be administered until *VAS* ***=*** *0*. Once VAS = 0, analgesics will be discontinued. Treatments not mentioned in this protocol will not be allowed unless approved and standardized by the research team. All unmentioned treatments will be recorded thoroughly by the research assistants.

### Provisions for post-trial care {30}

Hyponatremia, delirium and haemodynamic instability during the study period are anticipated for the participants of this trial.

### Outcomes {12}

#### Primary outcomes

The primary outcome is the preventive efficacy of PHN, which will be measured based on a 100 mm VAS in which 0 mm represents no pain and 100 mm represents the most severe pain imaginable. Any pain scores other than 0 mm on the VAS 12 weeks after HZ onset will be defined as PHN.

#### Secondary outcomes

Average weekly VAS scoreAverage weekly consumption per analgesicsWeekly feature of the painQuality of life (QoL) based on the 12-item Short-Form Health Survey (SF-12) [28] upon completion of weeks 4, 8 and 12Patient Global Impression of Change Scale (PGIC) [29] at week 12Sleep quality as measured by the Pittsburgh Sleep Quality Index (PSQI) [30] self-rated questionnaire upon completion of weeks 4, 8 and 12

### Participant timeline {13}

Participant timeline is shown in Table 1.

**Table 1 Tab1:**
[figure not shown]
Time schedule of participant enrolment, allocation and assessment

*VAS* visual analogue scale, *QoL* quality of life, *SF-12* 12-item Short-Form Health Survey, *PGIC* Patient Global Impression of Change Scale, P*SQI* Pittsburgh Sleep Quality Index, *D* day, *W* week

### Sample size {14}

Based on the reported prevalence, the incidence of PHN in China is approximately 30% [2] after VZV reactivation. We predict that the same incidence will be observed in participants from the control arm. For participants in the duloxetine arm, the preventive protocol is expected to reduce the incidence to 20%. Assuming a 15% rate of loss to follow-up, a total of 750 participants would provide 90% power to detect the significant difference in the incidence of PHN using a 2-tailed alpha of 0.05.

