## Introduction

### Background and rationale {6a}

Postherpetic neuralgia (PHN) is the most common complication attributed to herpes zoster (HZ), which involves the reactivation of residual varicella zoster virus (VZV). Although the definition varies, pain that persists for 4 weeks to 6 months following acute HZ onset is recognized as PHN. Risk factors [1] for the development of PHN include older age, skin damage and pain intensity during acute HZ. In China, the prevalence of HZ is reported to be 7.7% [2] among the adult population, and an estimated 2.77 [3] million cases are diagnosed annually. Among those cases, 30% [2] are predicted to develop PHN after 12 weeks. Recent investigation [4] has shown that PHN is associated with sleep disturbances, lower quality of life, restricted daily activities and increased medical costs, all of which impose heavy burden on the patient and their finances. In addition, neuropathic pain [5] often persists for months or years and is refractory to drugs. Although a group of medications such as antidepressants, antiepileptics and topical agents are recommended by international guidelines, management of PHN is still challenging. Current therapeutic modalities fail to meet clinical expectations, as significant pain relief is achieved in less than 50% of patients [6] even with the most effective medications for PHN. Preventive and pre-emptive management [7] has been advocated for PHN in the future.

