### Eligibility criteria {10}

Patients presenting to the Department of Emergency, Dermatology, Neurology or Pain Management at any participating centre will be screened for eligibility to join the present study. Patients aged more than 50 years who are diagnosed with uncomplicated HZ, present with vesicles within 72 h of their emergence, and have an average pain score of at least 40/100 mm on a visual analogue scale (VAS, 0 = no pain, 100 = worst possible pain, at opposite ends of a 100-mm line) will be considered to fulfil the inclusion criteria. Patients who refuse to participate in the study or to provide written informed consent; those who have a raw score of more than 50 points on the Zung Self-Rating Depression Scale [26]; those who are confirmed to have HZ with head, neck, ocular, mucous membrane, cranial nerve, or central nervous system involvement or generalized HZ; those who are observed to have haemorrhagic or necrotizing lesions, satellite lesions, abnormal vesicles or acute retinal necrosis; those who have been on immunosuppressive therapy or mono- or multi-pharmacotherapy that involves any tricyclic antidepressant, valacyclovir, duloxetine or cytotoxic medications before acute HZ onset; those who have been diagnosed with hepatic, renal or immune dysfunction; those who are pregnant or breastfeeding; those with recorded hypersensitivity to the study drugs; those with contraindications to valacyclovir or duloxetine; and those who have been immunized with the HZ vaccination will be excluded from the study. Prior to the initiation of this study, research assistants (at least 2 research assistants per centre) will be trained regarding the details of this study protocol to ensure that the work would proceed smoothly. When patients are identified and diagnosed with acute HZ, research assistants will be informed and asked to screen the patients for eligibility. Eligible patients who are willing to participate will be recruited for the study.

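### On its own inputs the sample of 750 gives about 83% power, not the stated 90%, and that figure rests on a 30% control rate carried over from herpes zoster cases in general

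*Protocol article*

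**What the plan says.** Sample size {14} starts from a national figure: "the incidence of PHN in China is approximately 30% [2] after VZV reactivation". It carries this to the trial without adjustment: "We predict that the same incidence will be observed in participants from the control arm". The duloxetine arm is expected to reach 20%. With 15% lost to follow-up, 750 participants are said to give 90% power "using a 2-tailed alpha of 0.05". Trial design {8} sets 1:1 allocation, and Statistical methods {20a} names the chi-squared test for PHN incidence at week 12.

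Background and rationale {6a} shows where the 30% comes from. It gives the prevalence of herpes zoster among adults and the number of cases diagnosed annually in China, then says: "Among those cases, 30% [2] are predicted to develop PHN after 12 weeks". No age or pain restriction is attached. The same section says that risk factors for PHN "include older age, skin damage and pain intensity during acute HZ".

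Eligibility criteria {10} admits only patients aged more than 50 with uncomplicated herpes zoster who "have an average pain score of at least 40/100 mm on a visual analogue scale". The primary outcome is defined in Outcomes {12}: "Any pain scores other than 0 mm on the VAS 12 weeks after HZ onset will be defined as PHN".

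**The concern.** Two things are wrong with the power statement, and they are separate.

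The first is arithmetic. The inputs printed in {14} do not give 90% power at 750 participants. This is true whatever one thinks of the control rate.

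The second is the control rate. The protocol selects participants on two of the three PHN risk factors that it names, then predicts the rate seen in unselected cases and does not say why. The control rate is one of the two proportions that fix the power, so an unsupported value leaves the power unsupported too.

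At stake is how a result is read. If the true power is nearer 83% than 90%, the chance of missing the assumed effect is about 17% rather than 10%. If the control rate is not 30%, the chance could be larger or smaller, and {14} gives the reader no means of telling.

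**Working it through.** **Inputs.** From {14}: p1 = 0.30, p2 = 0.20, two-sided alpha 0.05 (z = 1.960), power 90% (z = 1.282), loss 15%, total 750. From {8}: 1:1 allocation. From {20a}: chi-squared test.

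**Step 1: sample size that the inputs require.** With p̄ = 0.25,

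n per arm = [1.960·√(2·0.25·0.75) + 1.282·√(0.30·0.70 + 0.20·0.80)]² / 0.10²
= [1.960·0.6124 + 1.282·0.6083]² / 0.01 = 1.980² / 0.01 ≈ 392.

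That is 784 evaluable, and 784/0.85 gives 923 enrolled. Other usual formulas do not come near 750: unpooled variance gives 916, arcsine 920 and continuity correction 970. Multiplying by 1.15 instead of dividing by 0.85 still gives 895 or more.

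**Step 2: power at 750.** Evaluable per arm = 750·0.85/2 = 318.75.

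Power = Φ{[0.10·√318.75 − 1.960·0.6124] / 0.6083} = Φ{(1.785 − 1.200)/0.6083} = Φ(0.962) = 0.832.

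With no loss at all (375 per arm), power is 0.887, still short of 90%.

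**Step 3: can 750 be reproduced?** A one-sided alpha of 0.05 gives 320 per arm, 640 evaluable and 640/0.85 = 753 enrolled. This is close to 750 but contradicts the two-tailed alpha that {14} states.

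**Step 4: dependence on the control rate.** The documents give no rate for patients over 50 with VAS of at least 40 mm, so every control rate below other than 30% is an assumption. Evaluable participants stay at 318.75 per arm, with two-sided alpha 0.05.

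| Control rate | Rate under 10-point reduction | Power | Rate under one-third relative reduction | Power |
|---|---|---|---|---|
| 25% | 15% | 89% | 16.7% | 74% |
| 30% | 20% | 83% | 20% | 83% |
| 40% | 30% | 76% | 26.7% | 95% |
| 50% | 40% | 72% | 33.3% | 99% |

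The two readings of the effect agree only at 30%. At 40% they differ by about 19 percentage points of power (94.8% against 75.5%), and they move in opposite directions as the control rate changes.

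**The case against.** The strongest reply is that {14} names both proportions, which fully specifies the alternative. Stating two rates is ordinary practice, the absolute-or-relative question arises only once someone substitutes another control rate, and a condensed article may leave the justification of a planning rate to the full protocol. That is fair as far as it goes. It does not rescue the 90%, which is a printed figure that its own printed inputs contradict. Nor does it rescue the prediction of an unchanged rate, which is asserted in the article and sits badly with the risk factors listed there.

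A reader might go further and infer that the control rate will exceed 30%. The documents do not support that. Age and pain selection push upward, but other features may push downward. Eligibility criteria {10} excludes head, neck, ocular and generalized disease, haemorrhagic or necrotizing lesions, and immune dysfunction. Concomitant care {11d} gives valacyclovir and stepped analgesia to everyone. The background reports that PHN persisted despite antivirals, but it also says treatment of acute disease is believed to lower PHN incidence, so it cannot be cited as ruling out an offset. The Discussion figure of 61.8% to more than 70% is the share of PHN cases occurring over age 50, not the risk of PHN in patients over 50.

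A reader might also infer that the 30% counts a different event. Any non-zero VAS is the most inclusive threshold possible, and the background says PHN definitions vary. But the 12-week time point matches, and the threshold used in the cited source is not given. This can only be asked, not asserted.

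**Conclusion.** The concern holds in two parts of unequal firmness.

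The firm part is that {14} overstates power by about 7 percentage points: about 83% rather than 90% for 750 participants at 30% against 20%, with two-sided alpha 0.05, 15% loss and a chi-squared test. This rests only on the protocol's own inputs and a standard normal approximation. The match with a one-sided calculation is suggestive, but the documents do not show how 750 was derived.

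The softer part is that the 30% is a figure for herpes zoster cases in general, applied without explanation to patients selected on two risk factors that the protocol names. The documents fix neither the size nor the net direction of the resulting error. Over assumed control rates of 25% to 50%, power runs from 72% to 89% for a 10-point reduction and from 74% to 99% for a one-third relative reduction. The mismatch therefore makes the power uncertain; it does not show that the trial is further underpowered.

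**What to change.** All changes are to Sample size {14}.

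1. Replace the 90% with about 83% for the fixed 750 at 30% against 20%, two-sided alpha 0.05 and 15% loss.
2. Replace the sentence predicting an unchanged incidence with an expected control rate justified for the eligible population (over 50, VAS of at least 40 mm) and for the trial's own event (any VAS above 0 at 12 weeks). State the PHN definition behind the 30% so that a reader can see whether it is the same event.
3. Add a short table of power for the fixed 750 at control rates of 25%, 30%, 40% and 50%, marked as assumptions, with each column labelled as a 10-point absolute or a one-third relative reduction.

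The cost is a rewritten paragraph and a less favourable stated power. No additional patients and no change to the conduct of the trial are requested.

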### Trial design {8}

This PROCESS trial is a multicentric, randomized, open-label, blinded-endpoint study, designed to evaluate whether premedication with duloxetine within 72 h after VZV reactivation has a promising preventive effect on PHN. In total, 750 participants will be recruited from 18 different hospitals all over China. Participants will be assigned to either the duloxetine arm or the control arm in an allocation ratio of 1:1. The timeline and detailed schedule of the study are illustrated and summarized in Fig. 1.

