### Statistical methods

#### Statistical methods for primary and secondary outcomes {20a}

Statistical analyses will be performed using the SPSS 25.0 software package for Windows (SPSS, Inc., Chicago, IL, USA). The baseline and outcomes for the intervention will be compared to the control arm for primary analysis. Continuous variables will be expressed as the mean (SD) or median (IQR) and compared using Student’s *t* test or the Mann-Whitney *U* test. Normality will be tested using the Kolmogorov-Smirnov test. Categorical variables will be expressed as the number of patients (percentage) and compared using the chi-squared test or Fisher’s exact test. A 2-tailed alpha of 0.05 will be used as the threshold of statistical significance. The incidence of PHN in each arm at the end of week 12 will be compared using the chi-squared test. Subgroup analyses will be performed for age, gender, time to medication, maximum duloxetine dosage and average weekly pain score. Multiple logistic regression will be used to evaluate and determine the interference of the above confounding factors in the primary outcome. All analyses will be performed using both the intention-to-treat and per-protocol principles, and the final conclusion will be determined in line with the intention-to-treat principle.

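### The stated 90% power does not follow from the plan's own inputs: 750 participants with 15% loss give about 83% at two-sided alpha 0.05

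*Protocol article*

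**What the plan says.** All the inputs are in the protocol article.

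- **Event rates.** Sample size {14} takes a reported Chinese figure of about 30% as the control-arm rate and plans on 20% with duloxetine.
- **Size, loss and power.** The same section continues: "Assuming a 15% rate of loss to follow-up, a total of 750 participants would provide 90% power to detect the significant difference". Its alpha is 0.05, two-tailed.
- **What 750 counts.** Trial design {8} makes it the number enrolled, at 1:1: "In total, 750 participants will be recruited from 18 different hospitals all over China".
- **Test and sidedness.** Statistical methods for primary and secondary outcomes {20a} names the chi-squared test for PHN incidence at week 12 and repeats the sidedness: "A 2-tailed alpha of 0.05 will be used as the threshold of statistical significance".

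The document mentions no one-sided test.

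**The concern.** A two-sided comparison of 30% with 20% at 90% power needs more than 750 evaluable participants before any allowance for loss. A total of 750 that already includes a 15% loss therefore cannot give the stated power.

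The figure matters for interpretation. The Background attributes the missing 3-month effect in an earlier amitriptyline trial partly to limited sample size, and it presents a larger sample as part of the reason for this trial. A null result would be read against the 90% claim and taken as stronger evidence of no benefit than the design can supply.

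**Working it through.** **Inputs.** Control rate p1 = 0.30, duloxetine rate p2 = 0.20, loss 15%, 750 enrolled, 90% power and two-sided alpha 0.05 (Sample size {14}); 1:1 allocation (Trial design {8}); chi-squared test (Statistical methods {20a}). Hence the difference d = 0.10 and the mean rate p̄ = 0.25.

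**Terms of the pooled two-proportion formula**

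- Null term: √(2 × 0.25 × 0.75) = √0.375 = 0.6124
- Alternative term: √(0.30 × 0.70 + 0.20 × 0.80) = √0.37 = 0.6083
- z-values: 1.960 (two-sided 0.05), 1.645 (one-sided 0.05), 1.2816 (90% power)

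**1. Trying to reproduce 750 as stated (two-sided).**

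n per arm = [1.960 × 0.6124 + 1.2816 × 0.6083]² / 0.10² = (1.2002 + 0.7795)² / 0.01 = 391.9, so 392.

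Total evaluable 784; 784 / 0.85 = 922.4, so 923, or 924 with equal arms. The stated 750 is not reproduced.

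**2. Power that 750 gives.**

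Evaluable: 750 × 0.85 = 637.5, about 319 per arm.

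z = (0.10 × √319 − 1.2002) / 0.6083 = (1.7861 − 1.2002) / 0.6083 = 0.963, so power = 83.2%.

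With no loss (375 per arm): z = (1.9365 − 1.2002) / 0.6083 = 1.210, so power = 88.7%.

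**3. Does the choice of formula matter?** Two-sided 0.05 throughout:

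| Method | Power at 750 with 15% loss | Total enrolled for 90% |
|---|---|---|
| Pooled | 83.2% | 924 |
| Unpooled | 83.5% | 916 |
| Arcsine | 83.4% | 920 |
| Exact enumeration of the chi-squared test | 83.3–83.4% | not computed |
| Continuity-corrected | 80.8% | 970 |

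Inflating by × 1.15 instead of dividing by 0.85 gives totals of 896 to 948. None is near 750.

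**4. Which setting does give 750?** One-sided alpha 0.05:

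n per arm = (1.645 × 0.6124 + 0.7795)² / 0.01 = 319.3, so 320. Then 640 / 0.85 = 753 (754 with equal arms). Power at 319 per arm is 90.0%. Both the size and the power match.

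A two-sided 80% target does not match by the same formula: 294 per arm, 692 enrolled.

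**5. Effect for which 319 per arm gives 90% power.** For 30% versus 19%, p̄ = 0.245:

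z = (0.11 × √319 − 1.960 × √(2 × 0.245 × 0.755)) / √(0.21 + 0.1539) = (1.9647 − 1.1921) / 0.6032 = 1.281, so power = 90.0%.

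**The case against.** The strongest reply accepts the arithmetic and disputes its weight. The trial still has about 83% power at its target effect, above the commonly used 80%. The test, the alpha and the validity of the primary comparison are unaffected, and the difference detectable with 90% power moves only from 10 to 11 percentage points. That is a fair measure of the harm: the trial is usable. It does not make the printed 90% correct.

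The one-sided explanation is an inference, since the document claims no such calculation. Other slips come close: ignoring loss gives 88.7%, and a continuity-corrected two-sided calculation at 80% power with 15% loss gives 738. Each drops a stated input, as the one-sided route does. The one-sided route is the closest match and the only one of these that keeps both the 90% and the 15%. The error stands whatever its cause.

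The Study setting and Recruitment sections give 750 as a minimum, so more could be enrolled. Nothing commits the trial to about 924, and Trial design {8} gives 750 as the total.

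Nor does an intention-to-treat analysis of all 750 recover the power. If the 15% lost are counted as free of PHN, the rates become 25.5% and 17.0% and power at 375 per arm is 81.3%. If they are counted as PHN, the rates are 40.5% and 32.0% and power is 67.8%.

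A higher control rate is a side issue. Entry selects on age and acute pain, both named as risk factors in the Background, so a rate above 30% is plausible, but the document gives none. Taking 40% and 50% as assumptions, power at 319 per arm is 75.5% and 72.0% if the 10-point difference is held, but 94.8% and 99.0% if the risk ratio of 0.67 is held. The direction depends on the scale, so this adds nothing to the main point.

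**Conclusion.** The concern holds. On the plan's own inputs, 750 enrolled with 15% loss give about 83% power (80.8% to 83.5% across the methods checked), not 90%. The false-negative risk at the target effect is about 17% instead of 10%. The shortfall for 90% is about 174 enrolled (924 − 750).

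This rests only on the stated rates, loss, allocation, test and two-sided alpha, with lost participants left out of the comparison and loss equal in the two arms. That a one-sided alpha lies behind the 750 is likely but not shown by the document. The error is in the justification of the primary comparison and should be corrected, although it does not invalidate the design.

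**What to change.** In Sample size {14}, keep 750 and restate the power, for example: with 15% loss to follow-up, about 319 evaluable participants per arm give 83% power to detect 30% versus 20%, or 90% power to detect 30% versus 19%, at a two-sided alpha of 0.05.

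This is a wording change only. It costs a less favourable power figure and needs no further participants. If the sponsor prefers to keep 90% for 30% versus 20%, enrolment has to rise to about 924. The two-sided alpha in Statistical methods {20a} should stay as it is in either case.

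If registry, ethics or funding texts repeat the 90%, they need the same correction; those texts were not available here. A line on power at other control rates is optional. If one is added, it must say whether the absolute difference or the risk ratio is held constant.
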